## Abstract

**Introduction:**

Relationships between exacerbations of chronic obstructive pulmonary disease (COPD) and environmental factors such as temperature, humidity and air pollution are not well characterised, due in part to oversimplification in the assignment of exposure estimates to individuals and populations. New developments in miniature environmental sensors mean that patients can now carry a personal air quality monitor for long periods of time as they go about their daily lives. This creates the potential for capturing a direct link between individual activities, environmental exposures and the health of patients with COPD. Direct associations then have the potential to be scaled up to population levels and tested using advanced human exposure models linked to electronic health records.

**Methods and analysis:**

This study has 5 stages: (1) development and deployment of personal air monitors; (2) recruitment and monitoring of a cohort of 160 patients with COPD for up to 6 months with recruitment of participants through the Clinical Practice Research Datalink (CPRD); (3) statistical associations between personal exposure with COPD-related health outcomes; (4) validation of a time-activity exposure model and (5) development of a COPD prediction model for London.

**Ethics and dissemination:**

The Research Ethics Committee for Camden and Islington has provided ethical approval for the conduct of the study. Approval has also been granted by National Health Service (NHS) Research and Development and the Independent Scientific Advisory Committee. The results of the study will be disseminated through appropriate conference presentations and peer-reviewed journals.

Strengths and limitations of this studyThis study will allow researchers to assess associations in far more detail, initially at the individual patient level and potentially at a national level.It will demonstrate the integration of novel methodological approaches in three main areas: (1) the recruitment of participants via an anonymised general practice records database, and use of electronic health records to gather information on chronic obstructive pulmonary disease (COPD) exacerbations; (2) mass deployment of portable air quality sensor platforms over long periods revolutionising the way in which personal exposure can be quantified and (3) the application of a dynamic human exposure model.Much of the success depends on participant participation over a long period (up to 6 months) and there may be difficulties with recruiting enough participants to power the study.Physiological and inflammatory changes are not being recorded as part of this study; however, these issues will be addressed in this protocol and will be examined in a substudy of characterisation of COPD exacerbations using environmental exposure modelling.

## Introduction

Chronic obstructive pulmonary disease (COPD) is a chronic progressive disease associated with the abnormal inflammatory response of the lungs to noxious particles or gases^1^ and is characterised by increased resistance to airflow in small conducting airways, changes in lung compliance and the premature collapse of airways during expiration.^2^ The inflammatory responses can lead to increased sputum production, breathlessness and reduced lung function, often resulting in reduced exercise tolerance and decreased quality of life.^3^
^4^ COPD has a large burden on healthcare resources with an estimated annual cost to the National Health Service (NHS) currently of over £800 million.^5^ At present, it is the fourth leading cause of death worldwide, and it is predicted that total deaths from COPD may increase by more than 30% in the next 10 years unless urgent action is taken to reduce the underlying risk factors.^6^

Smoking is the most important risk factor for COPD; however, an estimated 25–45% of patients have never smoked. Other risk factors include a history of pulmonary tuberculosis, chronic asthma, childhood respiratory tract infections, occupational exposure to dusts and gases, air pollution and low socioeconomic status.^7^ The prevalence of COPD is increased in individuals living close to traffic,^8^ and patients with COPD have substantial mortality risks associated with particles^9^ and temperature changes.^10–12^ Exacerbations of COPD are acute episodes of deterioration associated with increased mortality and decreased quality of life, and are the second most common cause of adult emergency medical hospital admission in the UK.^8^ Infections, both bacterial and viral, are known to play a major role in exacerbations.^4^

Gaps still exist in our understanding of the mechanisms involved in exacerbations and the particular air pollutants and environmental conditions that lead to increased hospitalisations. Previous systematic reviews and meta-analytic studies have found small but significant effects of particulate matter (PM_10_ and PM_2.5_) and gases such as ozone (O_3_) and nitrogen dioxide (NO_2_) on COPD-related admissions and mortality.^13–17^ However, such findings are only indicative, as the evidence comes from a relatively small number of time-series and case-crossover studies with significant heterogeneity between them. The methodological design of those studies introduced additional limitations in the interpretability of the findings stemming from the inability to accurately characterise exposure to air pollutants at the individual level. Such critical limitations have been the absence in most studies of detailed activity patterns, the reliance on aggregated health counts and the low spatiotemporal resolution of air pollution from a small number of fixed monitoring sites resulting in the inadequate adjustment for confounders and covariance between air pollutants.

Consequently, there has been a continued effort to understand the relationship between ambient concentrations and personal exposure. Personal exposure assessment requires the recording of a person's time-activity patterns, as well as the pollutant concentrations which each individual is exposed to. At the most basic level, this may be the relative proportion of time spent in different microenvironments. Additionally, activity type of individuals may affect indoor air pollution levels, while activity levels may alter dose. Estimating personal exposure has been challenging, because of the expense and availability of personal monitors, as well as the lack of detailed information at the individual level which is limited by the accuracy of time-activity diaries, which can be laborious, introduce recall biases and reliability, and require active cooperation of the participants in the monitoring process, often limiting their application in small panel studies.

This research is timely as it brings together recent advancements in technological aspects of personal air quality monitors and computational developments to create detailed hybrid models of personal exposure. This paper presents the integrated methodological framework which will be used for the ‘characterisation of COPD exacerbations using environmental exposure modelling’ (COPE) study. This research project takes the first steps towards the integration of novel methodological approaches in three main areas : (1) the recruitment of participants via an anonymised general practice records database, and use of primary care electronic records to gather information on COPD exacerbations; (2) mass deployment of portable air quality sensor platforms over long periods revolutionising the way in which personal exposure can be quantified with automated classification of individual time-activity patterns and exposure events and (3) the application of a dynamic human exposure model. Together, these have the potential to provide powerful tools to create and validate accurate personal exposure models with higher spatiotemporal resolution, allowing, for the first time, the incorporation of spatially realistic exposure models in epidemiological studies.

## Methods and analysis

A series of five work packages move through a number of phases, from instrument development and recruitment, through cohort monitoring and analysis, to predictive model development (figure 1).

**Figure 1 BMJOPEN2016011330F1:**
[figure not shown]
Project flow diagram. COPD, chronic obstructive pulmonary disease; CPRD, Clinical Practice Research Datalink; RH, relative humidity.

### Development and long-term deployment of personal air pollution sensors

Personal air monitors (PAMs) have been designed, manufactured and tested specifically for the COPE study (figure 2). The PAMs can be either strapped around the waist with a belt or worn over the shoulder. A waterproof case will be provided to the participants to make it less conspicuous when worn outside the house. The PAMs will employ ubiquitous sensing of a large number of geotemporal environmental parameters that can be measured simultaneously (table 1). The measurements will be stored in the sensor and uploaded through General Packet Radio Service to a secure server through the charging base station. No interaction with the unit is required by the participant, other than to place it in its charger each night (the battery life of the sensor is 30 hours between charges). It will operate continuously and is almost silent.

**Table 1 BMJOPEN2016011330TB1:** Summary of monitored parameters of the PAMs

Parameter	Method	Monitoring interval
Spatial coordinates	GPS	20 s
Background noise	Microphone	100 Hz
Physical activity	Triaxial accelerometer	100 Hz
Temperature (°C)	Thermocouple	20 s
RH (%)	Electrical resistive sensor	20 s
PM_1_, PM_2.5_, PM_10_ (μg/m^3^)	OPC	20 s
CO, NO, NO_2_, O_3_ (ppb)	Electrochemical sensors	20 s

CO, carbon monoxide; GPS, Global Positioning System; NO, nitric oxide; NO_2_, nitrogen dioxide; OPC, optical particle counter; O_3_, ozone; PAM, personal air monitor; PM, particulate matter; ppb, parts-per-billion; RH, relative humidity.

**Figure 2 BMJOPEN2016011330F2:**
[figure not shown]
Design of the PAM platform internals, in charging base-station and ‘en masse’. PAM, personal air monitor; RH, relative humidity; SD, secure digital.

In order to reduce transmission costs and the computational burden of the portable device, transmitted data from the accelerometer and microphone will be reduced by event counting within 20 s non-overlapping windows. Spatial points resulting from Global Positioning System (GPS) coordinate errors were identified and have been removed based on Euclidean distance and earth bearing between consecutive points.

The selected gases (NO_2_, O_3_, NO and CO) will be quantified with electrochemical sensors based on amperometric methods at parts-per-billion (ppb) mixing ratios. Once appropriate calibration factors and postprocessing have been applied to sensor data, excellent sensitivity can be achieved in laboratory and field settings.^18^ The PAM incorporates a miniaturised optical particle counter that will record particle counts in 16 particle sizes (bins) in the range from 0.35 to >17 μm. The bins will then be aggregated to estimate the mass of the three fractions PM_1_, PM_2.5_ and PM_10_.

### Participant recruitment and monitoring

#### Recruitment of panel participants

Traditionally, recruitment for observational studies involves time-consuming and labour-intensive contact with suitable participants that meet the inclusion/exclusion criteria. In this study, we employ a novel method of recruitment that involves approaching GPs and patients to participate through the Clinical Practice Research Datalink (CPRD), an anonymised general practice records database containing ongoing primary care medical data. This method of recruiting for observational and interventional studies has been shown to be effective in a pharmacogenetic study;^19^ and in a cluster randomised control trial on asthma exacerbation among school-aged children.^20^ Apart from the efficiency in recruiting participants, this method can also be considered broadly representative of the UK general populations with coverage of over 11.3 million patients and 674 practices.^20^ An additional benefit is that once participants are recruited, the anonymous data from electronic health records (EHRs) can be linked to diverse parameters collected simultaneously (eg, data from air quality monitors/mobility data) to provide detailed clinical information about the study participants.

In total, 160 participants will be recruited from CPRD using an algorithm containing validated COPD diagnostic codes. Patients with data in CPRD who have a diagnosis of COPD based on a validated code list by Quint *et al*^21^ are not coded for mild COPD (ie, moderate or severe patients only), are not coded as a current smoker, are aged >35 years, and have had between one and two identified exacerbations in the preceding year will be included. After running the algorithm to identify suitable participants, general practices that have agreed to participate in research through CPRD will be sent a list of the potential participants. GPs will confirm to CPRD the suitable patients identified previously using the Vision Identification. CPRD will then send participant information packs to the general practices to disseminate to the potential recruits. The information pack will contain a cover letter from the general practitioner introducing the study, a participant information sheet with detailed information of what the project entails, and an expression of interest form that participants can complete and send to the research team in a prepaid envelope. Once received, the research team will then be able to contact the participant to enrol them in the study through a clinic appointment. Participants will also be recruited from respiratory clinics in secondary care as an additional recruitment option.

The sample size of 160 patients is based on the estimated number of exacerbations for the cohort. Since we will recruit with a bias towards patients with COPD with a history of COPD exacerbations, we have made the conservative estimate that we will capture at least 200 exacerbations with a cohort of 160 patients. We have calculated a minimum detectable relative risk (RR) to detect associations at p<0.05 with 80% power. With 200 exacerbations, this will permit detection of about RR=1.65 in the highest 20% of days compared with others (RR=2.00 in the highest 10%). Other more common outcomes and in particular peak flow will have power to detect smaller associations.^22^

Two secondary recruitment methods will be established to make up any shortfall in recruits through the CPRD: recruitment from respiratory clinics in local hospitals and presentations at British Lung Foundation ‘Breathe Easy’ respiratory disease support groups.

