#### Monitoring phase

At the clinic, participants will be provided with a PAM and instructed to keep the monitor at home and take it out with them for a minimum of once a week for up to 6 months. An initial questionnaire will collect information on lifestyle factors and residence characteristics, such as type of cooker used in the home (eg, gas, electric or wood burning stove) and car ownership. During the study period, participants will complete daily diary cards of their symptoms, any changes to their treatment (eg, medications) and sleep disturbance. They will be asked to record their peak expiratory flow on the diary card using a peak flow meter. Spirometry readings will be collected at the initial appointment and subsequent follow-up visits if the participant consents. This will provide information on the severity of their condition and may control for possible random differences.

If at any stage the wearing compliance of the PAM is low, or the participant chooses to withdraw, a replacement will be recruited. Throughout the monitoring period, participants will receive phone calls from the research assistant to check how they are coping with the study. Six weeks into the monitoring period, participants will be invited to attend a clinic with the research assistant to discuss any issues with the PAMs or diary cards. At the end of the monitoring period (at 6 months or earlier if the participant wishes to withdraw), participants will be invited to a final appointment to return the PAMs and completed diary cards.

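### The upper limit of two prior-year exacerbations for CPRD recruits works against the 200-event target, which needs 2.5 exacerbations per patient-year

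*Protocol article*

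**What the plan says.** All of the following is in the Protocol article.

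- **Eligibility (Recruitment of panel participants).** Patients with data in CPRD who meet the diagnostic, severity, smoking and age conditions and who "have had between one and two identified exacerbations in the preceding year will be included". CPRD patients with none, or with three or more, are therefore not eligible. No reason for the upper limit is given.
- **Event count (same section).** The justification opens "Since we will recruit with a bias towards patients with COPD with a history of COPD exacerbations" and continues "we have made the conservative estimate that we will capture at least 200 exacerbations with a cohort of 160 patients".
- **Power (same section).** The calculation is "to detect associations at p<0.05 with 80% power". With 200 exacerbations the detectable RR is given as about 1.65 for the highest 20% of days and 2.00 for the highest 10%.
- **Duration (Abstract, Methods and analysis).** The plan is "monitoring of a cohort of 160 patients with COPD for up to 6 months".
- **Other routes (Recruitment of panel participants).** "Two secondary recruitment methods will be established to make up any shortfall in recruits through the CPRD". These are hospital respiratory clinics and patient support groups, and no exacerbation criterion is stated for them.
- **Leavers (Monitoring phase).** "If at any stage the wearing compliance of the PAM is low, or the participant chooses to withdraw, a replacement will be recruited". The number expected is not given.
- **Analysis (Statistical analysis).** Cox-type survival analysis for repeated measurements, each participant a stratum, with a robust sandwich covariance.

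**The concern.** The sample size rests on the number of exacerbations, not on the number of patients. In a conditional analysis with each participant as a stratum, someone with no exacerbation during monitoring adds nothing to the exacerbation hazard ratio. The minimum of one prior exacerbation selects patients likely to have an event. The maximum of two turns away the CPRD patients who would be expected to have the most, if past counts predict future ones. The article makes that same inference when it uses exacerbation history to support the 200.

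The analysis does not need the limit, since it accommodates several events per participant. Nor does the limit save monitors or visits. It also narrows a recruitment pool that the article fears may be too small, both in its strengths and limitations and in its Discussion.

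At stake is whether the exacerbation analysis, which is also the basis of the London prediction model, can detect the stated effects.

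**Working it through.** **Inputs from the article.** 160 patients; 200 events; at most 0.5 year each; p<0.05 (two-sided assumed, since sidedness is not stated); 80% power; exposed share of days q = 0.20 or 0.10; RR 1.65 or 2.00; prior-year count 1 or 2.

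**1. Reproducing the stated figures.** Schoenfeld events: D = (1.960 + 0.842)² / [q(1−q)(ln RR)²].
- RR 1.65, q = 0.20: 7.849 / (0.16 × 0.2508) = 196 events. At 200 events, power is 80.9% and the minimum detectable RR is 1.64.
- RR 2.00, q = 0.10: 7.849 / (0.09 × 0.4805) = 182 events. At 200 events, power is 83.7% and the minimum detectable RR is 1.94.

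The first stated figure is reproduced. The second is rounded up on the safe side. The formula is sound given 200 events, so the question is the 200.

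**2. Rate implied by 200 events.** 200 / 160 = 1.25 per patient; 1.25 / 0.5 year = 2.5 per patient-year. This is 25% above the highest prior-year count the CPRD criterion allows.

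**3. Yield within the eligible range.** Assumptions: the follow-up rate equals the prior-year rate, and all 160 complete 6 months. Events = 160 × rate × 0.5. Power = Φ(√[D q(1−q)] × ln RR − 1.960). Minimum detectable RR = exp{2.802 / √[D q(1−q)]}.

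| Rate per year | Events | Power, RR 1.65, top 20% of days | Detectable RR, top 20% | Power, RR 2.00, top 10% of days | Detectable RR, top 10% |
|---|---|---|---|---|---|
| 1 | 80 | 43% | 2.19 | 46% | 2.84 |
| 1.5 | 120 | 59% | 1.90 | 62% | 2.35 |
| 2 | 160 | 72% | 1.74 | 75% | 2.09 |
| 2.5 (needed) | 200 | 81% | 1.64 | 84% | 1.94 |

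**4. Effect of dropping the upper limit.** The article gives no event rates by prior count, so rates are assumed: each patient's rate is gamma with mean m and shape k, and counts are Poisson. Given n prior-year events, the expected rate is (k + n) / (k/m + 1).
- For m = 1.0 per year and k = 1, the mean rate is 1.17 with one or two prior events, 1.50 with at least one, and 2.50 in the excluded group with three or more.
- Over 160 × 0.5 = 80 patient-years this gives 93 against 120 events, a gain of 29%.
- Over m = 0.7, 1.0, 1.5 and k = 0.5, 1, 2, the gain runs from 8% (m = 0.7, k = 2) to 88% (m = 1.5, k = 0.5). The limit excludes 12% to 41% of patients with at least one prior event.
- Without the limit, only one of the nine combinations reaches 200 (210 at m = 1.5, k = 0.5). The other eight give 74 to 168.

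**The case against.** A reader might infer that the criterion contradicts the stated bias towards patients with an exacerbation history, or that it excludes frequent exacerbators. The article supports neither reading. A minimum of one prior-year exacerbation removes patients with none, so every CPRD recruit has the history described. The article does not define a frequent exacerbator and never says it seeks them. Patients with two are admitted, and only those with three or more are shown to be excluded. The limit is also written only for patients with data in CPRD.

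Bounding prior event counts is an ordinary eligibility choice. It spreads events over more participants, and it may suit a prediction model built on typical patients' activity patterns. A journal article may leave the reason to the full protocol, so the missing rationale carries little weight by itself.

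On size, the 8% to 88% gain rests on assumed rates and runs from trivial to large. Prior events are those identified in records, whereas the study also keeps daily diaries and replaces leavers, so observed rates could be higher. To reach 200, capture would have to be 1.25 times the record-based rate at 2 per year and 2.5 times at 1 per year. The article gives no such factor. A one-sample binomial calculation is kinder: 160 events would give about 80% power for RR 1.65. But it needs only 161 and 125 events for the two stated RRs, so it does not reproduce the article's figures, and it still gives 53% and 69% at 80 and 120 events.

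These points rule out the stronger readings and limit how precisely the gain can be stated. They do not explain how a cohort selected at one or two exacerbations a year yields 2.5 a year.

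**Conclusion.** The point holds as a mismatch between an eligibility limit and an event target. The 200 events need 2.5 exacerbations per patient-year. The CPRD criterion selects patients at 1 to 2 per year, which gives 80 to 160 events and 43% to 72% power for RR 1.65 in the highest 20% of days. On the article's own figures, at least 200 is not a conservative estimate.

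This rests on follow-up rates matching the prior year, full 6-month follow-up, two-sided testing and Schoenfeld's formula. Shorter follow-up without replacement would lower the yield; diary-detected events or extra person-time from replacements could raise it by an unstated amount. The direction of the limit's effect depends only on past counts predicting future ones. Its size depends on rates that the article does not give.

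**What to change.** Change the CPRD criterion to at least one identified exacerbation in the preceding year. The participant-stratified repeated-event analysis already accommodates this. If the upper limit is kept, state its reason.

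In either case, reconcile the 200 with the eligibility range. State the assumed rate per patient-year, the expected follow-up, any factor for diary-detected events and the allowance for replacements. Then restate the expected events and the minimum detectable RR; at 120 events, for example, it is about 1.90 for the highest 20% of days. Dropping the limit alone should not be presented as securing 200 events.

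The cost is a small edit to the search algorithm and a notified amendment, and the eligible pool widens. The drawback is that more events fall in fewer patients, which the participant strata and the planned robust covariance handle.

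### The 200 exacerbations behind the power statement, called conservative, exceed the 80 to 160 expected from the article's own figures, and nothing stated bridges the gap

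*Protocol article*

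**What the plan says.** The Abstract (Methods and analysis) plans "recruitment and monitoring of a cohort of 160 patients with COPD for up to 6 months". Under Monitoring phase, follow-up ends "at 6 months or earlier if the participant wishes to withdraw". If a participant withdraws or wears the monitor too little, a replacement is recruited.

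Under Recruitment of panel participants, CPRD patients who "have had between one and two identified exacerbations in the preceding year will be included", subject to the other criteria. The same section bases the sample size on the number of exacerbations: "we have made the conservative estimate that we will capture at least 200 exacerbations with a cohort of 160 patients". The only reason it offers for this count is the way patients are chosen: "Since we will recruit with a bias towards patients with COPD with a history of COPD exacerbations". The target is "to detect associations at p<0.05 with 80% power", and with 200 events "this will permit detection of about RR=1.65 in the highest 20% of days compared with others (RR=2.00 in the highest 10" per cent of days).

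Under Use of EHR to analyse exacerbations, GP-treated exacerbations are to be identified from CPRD GOLD, with emergency and hospital admissions from linked records.

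**The concern.** The event count and the eligibility rule stand in the same section and do not fit together. A half-year of follow-up in patients who had one or two events over the previous full year points to fewer than 200 events from 160 patients. The only reason offered for 200 is enrichment for exacerbation history, but that enrichment is already contained in the figure of one to two per year.

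The sample size is justified by this count alone. If the count is too high, the detectable RRs for exacerbations are too favourable, and a null exacerbation result judged against them would look more informative than it is. The article warns of low power only through poor recruitment (Strengths and limitations; Discussion). A reader would not learn that full recruitment of 160 may also fall short. The associations with exacerbations are also meant to form the basis of the London prediction model.

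**Working it through.** **Inputs.** 160 patients and at most 6 months (Abstract; Monitoring phase); 1 to 2 exacerbations in the preceding year, 200 events, p<0.05, 80% power, and exposed shares of days p = 0.20 and 0.10 (Recruitment of panel participants). Sidedness is not stated; two-sided is assumed because it fits.

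**Step 1: reproduce the stated RRs at 200 events.** The authors' formula is not shown. The Schoenfeld form is

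RR = exp[(1.96 + 0.842) / √(E·p·(1−p))]

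- p = 0.20: √(200 × 0.16) = 5.657; 2.802 / 5.657 = 0.495; RR = 1.64 (stated 1.65). RR 1.65 needs 196 events.
- p = 0.10: √(200 × 0.09) = 4.243; 2.802 / 4.243 = 0.660; RR = 1.94 (stated 2.00). RR 2.00 needs 182 events.

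The first figure is matched closely and the second approximately. A one-sided version needs only 155 and 143 events, so it fits worse. The step from 200 events to the RRs is therefore sound.

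**Step 2: expected events from the article's inputs.** Person-time is 160 × 0.5 = 80 patient-years at most, with one monitored place per patient.

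- 1 per year: 80 events
- 1.5 per year (midpoint, for illustration): 120 events
- 2 per year: 160 events

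Rate needed for 200 events: 200 / 80 = 2.5 per patient-year. The stated 200 is 1.25 times the upper end of the range (200/160) and 2.5 times the lower end (200/80). At 1 to 2 per year, 200 events would take 200 to 400 patients for 6 months, or 7.5 to 15 months in 160 patients.

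**Step 3: consequence on the same formula.** Power = Φ(ln RR · √(E·p·(1−p)) − 1.96).

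| Events | Detectable RR, top 20% | Detectable RR, top 10% | Power at RR 1.65, top 20% | Power at RR 2.00, top 10% |
|---|---|---|---|---|
| 200 | 1.64 | 1.94 | 80.9% | 83.7% |
| 160 | 1.74 | 2.09 | 71.7% | 74.9% |
| 120 | 1.90 | 2.35 | 59.3% | 62.5% |
| 80 | 2.19 | 2.84 | 43.3% | 46.0% |

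**Step 4: sensitivity to the formula.** A one-sample binomial score test, with q = p·RR / (p·RR + 1 − p), gives these detectable RRs:

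| Events | Top 20% | Top 10% |
|---|---|---|
| 200 | 1.57 | 1.76 |
| 160 | 1.65 | 1.86 |
| 120 | 1.77 | 2.02 |
| 80 | 1.99 | 2.30 |

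At 160 events its power at RR 1.65 is 79.8%. This formula fits the stated pair at 200 events less well than Schoenfeld does.

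**The case against.** The strongest reply is that 80 to 160 is not a bound. The criterion limits the preceding year, not the rate during monitoring, and it is attached to patients with data in CPRD. The article does not say that it applies to recruits from respiratory clinics or support groups. Daily diaries and hospital records could capture more events than those used for selection, and replacements add person-time. All of this stands. A reader might infer that 200 is impossible or above a ceiling; the document does not support that.

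These routes do not rescue the claim, however. None is quantified or offered as the reason for 200. At 2 per year, 200 events need 100 patient-years, that is 20 more than 80, or about 40 extra full 6-month follow-ups. Study exacerbations treated by GPs come from the same database as the selection history, so carrying the prior rate forward compares like with like. Early withdrawal, and regression to the mean after selection on last year's count, pull the other way.

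Three other inferences should be resisted:

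- That withdrawal is ignored. Replacement is provided for; what is missing is any number attached to it.
- That the upper limit of two contradicts the intention to favour patients with an exacerbation history. Requiring at least one prior event is itself that enrichment, so there is no conflict and no case here for changing eligibility.
- That the stated RRs are missed under every method. At 160 events the binomial formula about reaches both.

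It is also fair to say that this is an observational panel study with other purposes, including validation of the exposure model. The article expects power for smaller associations with commoner outcomes such as peak flow, and this point does not touch that expectation.

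**Conclusion.** The point holds as a mismatch between the stated event count and the article's own inputs. The expected yield is 80 to 160 exacerbations against at least 200 claimed, and the word conservative is unsupported. On the formula that best matches the stated RRs, the design detects about 1.7 to 2.2 for the highest 20% of days and 2.1 to 2.8 for the highest 10%, and 80% power at 1.65 and 2.00 is missed across the whole range. On the less well-fitting binomial formula the stated RRs are about met at 160 events and missed at 80.

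This rests on three assumptions: the preceding-year rate carries forward, each of 160 places is monitored for the full 6 months, and study events are counted much as the selection events were. The fault lies in the event count and its description, not in the step from 200 events to the RRs.

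**What to change.** In the sample-size paragraph, do one of the following:

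- Remove the word conservative, give the expected events as 80 to 160, and restate the detectable RRs as about 1.7 to 2.2 (highest 20% of days) and 2.1 to 2.8 (highest 10%), naming the formula and the sidedness of the test.
- If 200 rests on a wider event definition, a higher rate in some recruits, or person-time from replacements, state that rate and its basis so that the count can be followed.

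Either way the change is to one paragraph. It needs no change to eligibility, cohort size or follow-up. The cost of the first option is a less favourable stated sensitivity for exacerbations.
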